### Assessments

The following will be assessed at the momento fo enrollment: age, sex, renal disease, Charlson comorbidity index, urine volume output in 24 h (mL), urea clearance (mL/min), creatinine clearance (mL/min).

The following will be assessed at the start of haemodialysis treatment (baseline) and every 2 months during a follow-up of at least 1 year: urine volume output in 24 h (mL), urea clearance (mL/min), creatinine clearance (mL/min), haemoglobin (g/dL), haematocrit (%), creatinine (mg/dL), urea (mg/dL), Na (mmol/L), K (mmol/L), albumin (g/dL), pre-albumin (mg/dL), calcium (mg/dL), phosphorus (mg/dL), parathyroid hormone (pg/mL), ferritin (ng/mL), beta-2 microglobulin (mg/L), brain-derived natriuretic peptide (pg/mL), C-reactive protein (mg/L), dose of dialysis (*Kt / V*), erythropoietin dosage (units per week per kg of weight), hydration, nutrition, hospital admissions, days of admission, causes of hospitalization and number of haemodialysis sessions.

The dose of dialysis is determined using the kinetic model of urea with the formulae modified from Gotch [22]. Dialysis *Kt* / *V* [3] is added to the residual renal function to give the total *Kt* / *V*:

Total *Kt* / *V* = dialysis *Kt* / *V* + (9.5 KrU) / *V* (for 2 haemodialysis sessions per week)

and

Total *Kt* / *V* = dialysis *Kt* / *V* + (5.5 KrU) / *V* (for 3 haemodialysis sessions per week),

where *V* is 58% of the dry weight (Watson formula) [23] and KrU is the residual urea clearance rate (mL/min).

Hydration and nutrition are measured by multi-frequency electrical bioimpedance (BCM®, Fresenius Medical Care). The following metrics are collected: overhydration (L), amount of extracellular water (L), amount of intracellular water (L), extracellular / intracellular ratio, body mass index (kg/m^2^), lean tissue index (kg/m^2^) and fat tissue index (kg/m^2^).

Quality of life will be assessed using the Kidney Disease Quality of Life Short Form at the start of haemodialysis treatment (baseline), at 6 months and at 12 months (close-out). This is a validated questionnaire for the haemodialysis population.

The schedule of enrolment, intervention and assessments is shown in Fig. 1.

**Fig. 1 Fig1:**
[figure not shown]
Schedule of enrolment, interventions and assessments * Patients receiving twice-weekly haemodialysis sessions are switched to the conventional arm if KrU < 2.5 mL/min/1.73 m^2^ in two determinations made in a 2-week interval, or if they develop uncontrolled hypertension, heart failure or a clinical event that indicates that the number of haemodialysis sessions should be increased. BNP brain-derived natriuretic peptide, CRP C-reactive protein, HD haemodialysis, KDQOL-SF Kidney Disease Quality of Life Short Form, KrCr creatinine clearance rate, KrU urea clearance rate, PTH parathyroid hormone

### Criteria for progression

The dialysis technique used for each patient (high-flow haemodialysis or haemodiafiltration online) will be maintained throughout the follow-up period. The 3HD group will start with three sessions lasting 3–3.5 h to achieve an adequate dialysis *Kt* / *V*. The 2HD group will start with two sessions of 4 h.

According to Casino and López [24], to obtain an equivalent renal urea clearance rate of 11 mL/min, the adequate dialysis *Kt* / *V* should be 1.6 or 1.2 for 2 sessions per week and 3 sessions per week, respectively. Modifications to the dialysis procedure, such as increasing the blood flow, bath flow, dialyzer surface or duration of the dialysis session, will be made if patients do not reach an adequate *Kt* / *V*.

Participants in the 2HD group will be switched to the 3HD group if their urea clearance rate falls below 2.5 mL/min/1.73 m^2^ in two determinations made in a 2-week interval, or they develop uncontrolled hypertension, heart failure, or a clinical event that indicates that the number of haemodialysis sessions should be increased.

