### Outcomes

The main outcome is loss of kidney function, defined as urine volume output less than 100 mL in 24 h, 12 months after the initiation of haemodialysis therapy.

The secondary outcomes are: (1) erythropoietin dosage, (2) beta-2 microglobulin concentration, (3) hydration and nutritional status, (4) concentrations of uremic toxins, (5) dialysis dose, (6) number and duration of hospital admissions, (7) mortality and (8) quality of life.

In addition, cost-efficiency will be assessed by recording the cost of haemodialysis sessions and the monthly consumption of erythropoietin.

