### Data collection and statistical analysis

The data collected will be stored in a database specially designed for this study using Access (Microsoft Office Access 2007). The data will be entered by a dedicated member of the project team, who will ensure the integrity and quality of the data. The statistical analyses will be carried out with the statistics program Stata v.14 [25].

We will perform a blind interim analysis when at least half of the patients have been recruited and followed for at least 1 year. We will stop the trial if the group difference in the main outcome is statistically significant at a significance boundary *p* < 0.0051. The final analysis with the whole trial population will be carried out at the end of the follow-up at a significance level of 0.04795.

For the univariate analysis of quantitative variables, we will check the normality of the data using the Kolmogorov–Smirnov test. Depending on the assumption of normality, the two arms will be compared using parametric tests (Student’s *t*-test) or nonparametric tests (Mann–Whitney *U* test). The associations of categorical variables with the two treatment groups will be assessed by chi-squared tests or Fisher exact tests, as appropriate.

The loss of renal function is evaluated by the diuresis in 24 h at 12 months after initiation of haemodialysis therapy, and it is dichotomized with a threshold of 100 mL in 24 h. A time-to-event analysis will estimate the probability of loss of kidney function in both treatment groups using the Kaplan–Meier method. Survival curves will be compared with log-rank tests. This survival analysis will be complemented with a proportional hazard model to estimate the hazard ratio of kidney function survival adjusted for any confounding factors to identify any imbalance in the baseline characteristics of the patients.

All analyses will be carried out in accordance with the intention-to-treat and per-protocol principles, assuming that in the worst case the losses to follow-up are a failure of the allocated treatment arm. In the final analyses, for the comparisons between the two treatment groups, the probability of rejecting the null hypothesis will be adjusted according to the O’Brien and Fleming method [26].

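### The secondary outcome of dialysis dose is a Kt/V whose scale depends on session frequency, so a between-arm test partly measures the schedule itself

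*Protocol article*

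**What the plan says.** All references are to the protocol article.

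- **Outcomes.** The secondary outcomes include "4) concentrations of uremic toxins, (5) dialysis dose". No scale or unit is given there.
- **Assessments.** "The dose of dialysis is determined using the kinetic model of urea", at baseline and every 2 months. Total Kt/V is dialysis Kt/V plus a residual term that changes with the schedule: "9.5 KrU) / *V* (for 2 haemodialysis sessions per week" and "5.5 KrU) / *V* (for 3 haemodialysis sessions per week". V is set at 58% of dry weight. The number of sessions is also recorded.
- **Criteria for progression.** For an equivalent renal urea clearance of 11 mL/min, the adequate dialysis Kt/V "should be 1.6 or 1.2 for 2 sessions per week and 3 sessions per week, respectively". The same section moves 2HD patients to three sessions when KrU falls below 2.5 mL/min/1.73 m² on two determinations, or on clinical grounds.
- **Data collection and statistical analysis.** For quantitative variables, "Depending on the assumption of normality, the two arms will be compared using parametric tests", or else by Mann–Whitney. Dialysis dose is not exempted. Analyses follow intention to treat as well as per protocol.

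**The concern.** A between-arm comparison needs a measure that means the same thing in both arms. Here the number recorded for dose depends on how many sessions a patient has each week, and session frequency is the randomised factor. The protocol itself says that two different Kt/V values, one per schedule, correspond to the same clearance. A test on that scale can be clearly significant when the arms do not differ on the clearance scale that the protocol uses to set its targets.

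The direction matters. The scale gives the higher figure to the arm with fewer sessions, in a trial whose Discussion calls it essential to establish that the incremental schedule is safe. Switching adds a second problem. A 2HD patient who moves to three sessions stays in the 2HD arm under intention to treat, but is from then on scored by the other formula and held to the other target. On target, the recorded dose falls as sessions are added.

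**Working it through.** **Inputs from the protocol article:** residual coefficients 9.5 and 5.5, and V = 0.58 × dry weight (Assessments); dialysis Kt/V of 1.6 and 1.2 at 11 mL/min (Criteria for progression); 44 patients per arm (Sample size). **Assumed, because not given:** dry weight 55–85 kg, KrU 2.5–4 mL/min, and an SD of Kt/V of 0.3–0.6.

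**The plan's own figures.** The values 1.6, 1.2 and 11 mL/min come from a cited source and are taken as stated. The 44 per arm reproduces from a difference of 0.33 − 0.18 = 0.15 and SD 0.25 (80.4% power); it is used here only for detectability.

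**1. Is the measure per session?** The words do not appear, but the formulae imply it. A weekly renal term would carry one coefficient for both schedules: 10,080 min per week gives 10.08 KrU/V. The coefficients here differ by schedule.

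**2. Dialysis Kt/V, both arms on target.** 1.6 − 1.2 = 0.40, or 33% higher in 2HD (1.6/1.2 = 1.33), at the same stated 11 mL/min.

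**3. Summed over the week.** 2 × 1.6 = 3.2 against 3 × 1.2 = 3.6. The sign reverses.

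**4. Total Kt/V, same patient characteristics in both arms.** The gap is 0.40 + (9.5 − 5.5) × KrU/V = 0.40 + 4 KrU/V.

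| Weight (kg) | V (L) | KrU (mL/min) | Two sessions | Three sessions | Gap |
|---|---|---|---|---|---|
| 70 | 40.6 | 2.5 | 1.6 + 0.585 = 2.19 | 1.2 + 0.339 = 1.54 | 0.65 |
| 85 | 49.3 | 2.5 | 2.08 | 1.48 | 0.60 |
| 55 | 31.9 | 4 | 2.79 | 1.89 | 0.90 |

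In the first row, 4 × 2.5/40.6 = 0.25 of the gap comes only from weighting the same kidney function differently.

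**5. Does multiplying by the number of sessions repair it?** No. The residual term becomes 2 × 9.5 = 19 KrU/V against 3 × 5.5 = 16.5 KrU/V, still unequal for the same kidney. In the first row the weekly sums are 4.37 and 4.62.

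**6. Switching.** If a share s of the 2HD arm is on three sessions and everyone is on target, the 2HD mean is 1.6(1 − s) + 1.2s and the gap is 0.40(1 − s): 0.20 at s = 0.5. A switched patient's residual term also falls by 1 − 5.5/9.5 = 42% at unchanged KrU.

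**7. Would a test pick it up?** With 44 per arm and two-sided 0.05, a gap of 0.40 has power of about 100%, 96% and 88% at SD 0.3, 0.5 and 0.6. At half switched (gap 0.20) power is 88%, 47% and 35%. The result therefore depends on how many have switched as well as on the dose delivered.

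**The case against.** **The test is inferred.** No sentence says that total Kt/V will be tested between arms, and an article may leave the derivation of a secondary outcome to a fuller document. This stands in part. But the article does fix how dose is determined, names it as an outcome, and gives a between-arm rule for quantitative variables without exception. Followed as written, that produces the comparison described.

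**The formulae are legitimate.** They may well be, for checking adequacy within a schedule. Nothing here disputes that use.

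**Stronger readings that the documents do not support:**

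- *That the delivered dialysis is identical in the two arms.* Only the equivalent renal urea clearance is stated to be equal; summed weekly dialysis Kt/V is not.
- *That the artefact is 0.65 by the protocol's own statement.* Only the 0.40 follows directly. The 0.65 needs an assumed weight and KrU, and it reads the 11 mL/min as dialysis alone, which the text does not settle.
- *That the trial will conclude that 2HD patients are better dialysed.* No passage proposes this. Dose is adjusted towards schedule-specific targets, and toxins, beta-2 microglobulin, hydration, admissions and mortality are separate outcomes that bear on safety.
- *That the stated targets are wrong.* A rough fixed-volume, single-pool calculation (V 40 L, no residual function, sessions of 4 h and 3.25 h) gives 10.6 mL/min for two sessions at 1.6 and 12.8 for three at 1.2, not equal values. The article does not give the model behind its figures, so this shows only that the answer depends on the conversion used. It does not rescue the comparison: in that calculation, too, per-session Kt/V ranks the schedules in the opposite order to clearance.

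**Conclusion.** The point holds in a limited form. As the article stands, dialysis dose is measured on a scale that depends on session frequency and falls under a generic between-arm test. On the protocol's own equivalence, two arms on target would differ by 0.40 in dialysis Kt/V with no difference in equivalent renal urea clearance. For total Kt/V the gap would be about 0.65 (0.60–0.90 over the assumed weights and KrU), conditional on the 11 mL/min being dialysis alone. Both figures assume that nobody in 2HD has switched; the gap shrinks in proportion to the share who have, and that share is not given.

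The measure being per session is implied rather than written, and the equivalence of 1.6 and 1.2 is taken as stated. This should be corrected, but it touches one of eight secondary outcomes and leaves the primary outcome and the sample size alone.

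**What to change.** Under Outcomes and Assessments, define the between-arm dose outcome on one frequency-independent scale. Equivalent renal urea clearance including residual function is the natural candidate, since the protocol already refers to it. State the conversion formula and every input it needs, and say whether the 11 mL/min includes residual function. Label the existing Kt/V formulae as per session, if that is what is meant, and present them descriptively by current schedule as an adequacy check.

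The cost is one derived variable, plus confirmation that its inputs are recorded. The article lists Kt/V, KrU and number of sessions but gives no conversion formula, and achieved session duration is not among the listed assessments, so this has to be checked rather than assumed. No change to the dialysis targets or to the switching rule is proposed.

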### Recruitment period

Patient recruitment began on 1 January 2017 and will be extended until the required sample size has been recruited to ensure the established statistical power has been reached. The minimum follow-up will be 1 year.

### Sample size

Considering the data published in observational studies [4, 5, 7] and assuming an average decrease in the glomerular filtration rate of 0.18 mL/min/month in the 2HD group and 0.33 mL/min/month in the 2HD group [7], with a standard deviation of 0.25, 44 patients should be recruited into each group to achieve a power of 80% in a two sided comparison of means with a usual significance level of 0.05.

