### Withdrawal criteria

Patients will be withdrawn from the study if they receive a renal transplant, die***,*** recover renal function or transfer to another facility or if they withdraw their informed consent.

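### The 44 per group is the number of fully evaluable patients for 80% power, but the plan states it as the number to recruit, with no margin for its own withdrawals

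*Protocol article*

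**What the plan says.** The Sample size section assumes an "average decrease in the glomerular filtration rate of 0.18 mL/min/month in the 2HD group" and "0.33 mL/min/month in the 2HD group" (the second label is evidently a slip for 3HD). It describes a "two sided comparison of means with a usual significance level of 0.05" and concludes, "with a standard deviation of 0.25, 44 patients should be recruited into each group to achieve a power of 80" percent. The Abstract gives the same number, power and significance level.

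Three other sections bear on this figure:

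- **Withdrawal criteria.** Patients leave the study on renal transplant or death, or if they "recover renal function or transfer to another facility or if they withdraw their informed consent".
- **Recruitment period.** Recruitment runs until the required number has been enrolled, and the section ties this to reaching the planned power. Follow-up is at least 1 year.
- **Data collection and statistical analysis.** There is one interim look with boundary p < 0.0051, and the final test is carried out "at the end of the follow-up at a significance level of 0.04795". Losses to follow-up are counted, in the worst case, as failures of the allocated arm.

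**The concern.** A power calculation returns the number of patients who must supply the analysed quantity. The plan uses that number as the enrolment target and also stops enrolment on it. Its own rules then remove patients during a follow-up of at least a year, and the Discussion says that patients with severe comorbidities are not excluded in advance. Under these rules the number recruited and the number evaluable can be expected to differ, and the sentence about power is true only if they coincide.

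What is at stake is the accuracy of the stated power. A reader, funder or ethics committee would take 80% as a property of a trial with 88 patients enrolled, when it belongs to a trial with 88 patients fully followed.

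**Working it through.** **Inputs from the Sample size section.** Difference δ = 0.33 − 0.18 = 0.15 mL/min/month; SD σ = 0.25; δ/σ = 0.60; two-sided alpha 0.05; power 80%. Allocation is 1:1 (Trial design). The interim and final significance levels are 0.0051 and 0.04795 (Data collection and statistical analysis).

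**Step 1: reproduce the plan's figure.**
n = 2 × [σ(z₀.₉₇₅ + z₀.₈₀)/δ]² = 2 × [0.25 × (1.960 + 0.842)/0.15]² = 43.60, rounded up to 44 per group.
This matches exactly, with no attrition term and at the unadjusted alpha. A t-test version gives 44.6, so 45, a difference of one patient that reflects the choice of approximation.

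**Step 2: power at 44 evaluable per group, single test at 0.05.**
θ = 0.60 × √(44/2) = 2.814; power = Φ(2.814 − 1.960) = 80.4% (t-test 79.5%).

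**Step 3: does the reduced final alpha matter?**
The critical values are 2.801 (p = 0.0051) and 1.978 (p = 0.04795). Taking the interim at half the information, Z₁ has mean θ√0.5, Z₂ has mean θ, and their correlation is √0.5.
Overall power = 1 − P(|Z₁| < 2.801 and |Z₂| < 1.978).

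- θ = 2.814 (44 per group, no loss): 80.04%.
- θ = 0 (no effect): 0.0499, so the two looks together use the nominal 5%.

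The final look on its own has 79.9% power (t-test 78.9%), but that leaves out trials that would already have stopped at the interim. The alpha split therefore does not cause a shortfall.

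**Step 4: effect of withdrawals.**
The document states no loss rate, so the rates below are assumptions. Each withdrawn patient is taken to contribute no GFR decline. Evaluable n per group = 44 × (1 − loss), and θ = 0.60 × √(n/2).

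| Assumed loss | Evaluable per group | Overall two-look power (normal) | Final look only, t-test at 0.04795 |
|---|---|---|---|
| 0% | 44 | 80.0% | 78.9% |
| 5% | 41.8 | 78.0% | 76.8% |
| 10% | 39.6 | 75.8% | 74.5% |
| 15% | 37.4 | 73.4% | 72.0% |
| 20% | 35.2 | 70.8% | 69.3% |

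There is no slack in the rounding: 43 evaluable per group already gives 79.1% over both looks.

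**The case against.** **The calculation is right as arithmetic.** It is: 44 reproduces exactly. The defect is that an evaluable number is presented as a recruitment number, with no allowance for loss.

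**The size rests on invented rates.** The document lists reasons for withdrawal but gives no rate, so only the direction of the shortfall is certain. The percentages show what follows from each assumed rate and are not estimates for this trial.

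**Withdrawn patients are not worthless.** This also stands. The sizing variable is a monthly rate, and the Assessments section schedules urea and creatinine clearance at baseline and every 2 months. A patient who leaves after several visits could supply a less precise rate. Treating such patients as wholly lost is the pessimistic end. The article, however, names no method that uses partial series: for quantitative variables it offers a t-test or a Mann–Whitney test.

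**Stronger readings that the document does not support.** A reader might infer that the 0.04795 final level, or the use of a t-test, is a second cause of lost power. Step 3 shows that overall power with no loss is still 80.0%, and the t-test difference is one patient per group. A reader might also infer that counting losses as failures lowers power further. That rule fits the urine-volume outcome and supplies no value for a mean GFR decline. Its effect on the main outcome has not been computed, and with unequal losses it could move the comparison either way.

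**The GFR comparison is not the main outcome.** True: the Outcomes section defines the main outcome as urine volume below 100 mL in 24 h. That mismatch is a separate question. It limits what a corrected power figure can tell the reader, so the corrected figure must be labelled accordingly.

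**Conclusion.** The point holds in this limited form: 44 recruited per group gives 80% power for the GFR-decline comparison only if nobody is lost, and the plan provides for five kinds of loss while stopping enrolment at 44. Under the pessimistic bound, the shortfall over both looks is about 2 points at 5% loss, 4 at 10%, 7 at 15% and 9 at 20%; a t-test at the final look alone is 1 to 2 points lower still. The results assume a difference of 0.15, an SD of 0.25, an interim at half the information, equal losses in the two arms and no contribution from withdrawn patients. With partial follow-up retained, the shortfall would be smaller by an amount the document does not allow one to compute. Nothing here shows how much power the trial has for its main outcome.

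**What to change.** In the Abstract and in the Sample size section, state that 44 is the number of evaluable patients per group. Replace the 80% with the power delivered at the sponsor's expected withdrawal rate, shown over a range of rates, with the source of the expected rate given. Label the figure as applying to the comparison of mean GFR decline only.

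Optionally, specify that this comparison will use a mixed model on all the 2-monthly clearance values, so that patients with partial follow-up stay in the analysis. These measurements are already scheduled, so the cost is a few lines of specification. How much power this would recover has not been calculated.

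The cost of the main change is a slightly less favourable stated power. It requires no additional patients.

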**Methods/design:**

This report describes the study protocol of a randomized prospective multi-centre open-label clinical trial to evaluate whether starting renal replacement therapy with twice-weekly haemodialysis sessions preserves residual renal function better than the standard thrice-weekly regimen. We also explore other clinical parameters, such as concentrations of uremic toxins, dialysis doses, control of anaemia, removal of medium-weight uremic toxins, nutritional status, quality of life, hospital admissions and mortality. Only incident haemodialysis patients who can maintain a urea clearance rate KrU ≥ 2.5 mL/min/1.73 m^2^ are eligible. Patient recruitment began on 1 January 2017 and will last for 2 years or until the required sample size has been recruited to ensure the established statistical power has been reached. The minimum follow-up period will be 1 year. Anuric patients with acute renal failure and patients who return to haemodialysis after a kidney transplant failure are excluded. It has been calculated that 44 patients should be recruited into each group to achieve a power of 80% in a two-sided comparison of means with a usual significance level of 0.05. A time-to-event analysis will estimate the probability of kidney function survival in both groups using the Kaplan–Meier method. Survival curves will be compared with log-rank tests. This survival analysis will be complemented with a proportional hazard model to estimate the hazard ratio of kidney function survival adjusted for any confounding factors. Analyses will be carried out in accordance with the intention-to-treat principle.

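### The stated 80% power is for a difference in mean GFR decline, which is not a named outcome; power for the main outcome (anuria, log-rank) is not established and cannot be derived from the protocol

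*Protocol article*

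**What the plan says.** Under Sample size, the trial is sized on GFR slopes: "assuming an average decrease in the glomerular filtration rate of 0.18 mL/min/month in the 2HD group" against "0.33 mL/min/month in the 2HD group", "with a standard deviation of 0.25". From these it concludes that "44 patients should be recruited into each group to achieve a power of 80% in a two sided comparison of means". The Abstract repeats the figure of 44 and the 80% and then turns directly to the time-to-event analysis.

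Under Outcomes, "The main outcome is loss of kidney function, defined as urine volume output less than 100 mL in 24 h", assessed 12 months after the start of haemodialysis. The eight secondary outcomes do not include GFR, urea clearance or creatinine clearance, although both clearances are measured every 2 months (Assessments).

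Under Data collection and statistical analysis, diuresis is dichotomised at 100 mL and analysed by Kaplan–Meier: "Survival curves will be compared with log-rank tests", with a proportional hazards model alongside. The final test is at 0.04795. Limitations again calls the main outcome anuria.

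Under Recruitment period, enrolment continues until the calculated size is reached, and the reason given is to secure the established power.

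**The concern.** The sample-size paragraph and the main analysis concern different variables and different tests. A t-type comparison of slopes uses each patient's whole decline. A log-rank test on a threshold event uses only the patients who cross the threshold, and when they cross it. Power for the first does not carry over to the second, even though the Discussion calls diuresis a proxy for residual renal function.

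This is not detail left to a fuller document. The article gives a complete basis for its sample size, and that basis does not match the outcome and test it names elsewhere. Two things are at stake. The figure of 44 decides when recruitment ends. And a non-significant anuria result would be read as coming from a trial with 80% power for that comparison, when no such power has been shown.

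**Working it through.** **1. The plan's own figure.** Inputs (Sample size): difference 0.33 − 0.18 = 0.15, SD 0.25, two-sided α 0.05, power 80%.

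n per group = 2(1.960 + 0.842)² × 0.25² / 0.15² = 43.6, rounded up to 44. Power at 44 is 80.4%. At the final level of 0.04795 it is 79.9% (45 per group for 80%), a negligible change. So 44 reproduces for a comparison of mean GFR decline.

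**2. What is missing for anuria.** Log-rank power needs a number of events and a hazard ratio, or an event rate in each arm. The protocol gives none of these. The slopes could be turned into event rates only with a baseline level, and the only baseline figure is the entry floor of KrU 2.5 mL/min/1.73 m².

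**3. Illustration from the plan's slopes.** Assumptions that are not in the protocol: slopes are normal, decline is linear, anuria occurs once a loss L has accrued, and the SD of 0.25 is entirely true between-patient variation. Then

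- P(anuria by 12 months) = P(slope > L/12)
- HR = ln(1 − p₂)/ln(1 − p₃), where p₂ and p₃ are the 2HD and 3HD rates
- events = 44(p₂ + p₃)
- power = Φ(½√events × |ln HR| − 1.978), where 1.978 is the critical value at 0.04795

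| Assumed L (mL/min) | Anuria 2HD vs 3HD | HR | Events | Power |
|---|---|---|---|---|
| 2.5 | 46% vs 69% | 0.52 | 50.2 | 63% |
| 4 | 27% vs 50% | 0.46 | 33.6 | 61% |
| 5 | 17% vs 36% | 0.42 | 23.6 | 56% |
| 6 | 10% vs 25% | 0.37 | 15.3 | 49% |
| 7 | 5% vs 16% | 0.32 | 9.2 | 39% |
| 8 | 3% vs 9% | 0.28 | 5.1 | 29% |

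**4. Simulated log-rank test, and how far it depends on the SD.** Settings: 44 per arm, visits every 2 months, α 0.04795, anuria at zero function, normal baseline with values below 2.5 set to 2.5, and 1,500 replicates (Monte Carlo error about 1.3 points). The baselines, the 12–36 month follow-up and the true slope SD of 0.15 are assumptions.

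| Baseline mean (SD) before the floor | SD 0.25, 12 months | SD 0.25, 12–36 months | SD 0.15, 12 months | SD 0.15, 12–36 months |
|---|---|---|---|---|
| 3 (0.5) | 66% | 69% | 97% | 98% |
| 4 (1) | 58% | 66% | 90% | 96% |
| 5 (1.5) | 49% | 63% | 73% | 94% |
| 6 (2) | 37% | 55% | 52% | 89% |
| 7 (2) | 32% | 55% | 34% | 85% |

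With the full SD of 0.25, every scenario falls between about 30% and 70%. With a true SD of 0.15 and the rest treated as measurement noise, power runs from 34% to 98%. The answer therefore turns on quantities the protocol does not state.

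**5. Illustration from a hazard ratio.** Taking HR = 0.18/0.33 = 0.545 (an assumption, since a ratio of slopes is not a hazard ratio), Schoenfeld's formula gives 4(1.960 + 0.842)²/(ln 0.545)² = 85.5, so 86 events (87 at 0.04795) from 88 patients. At assumed 3HD anuria rates of 30%, 50% and 70%, the expected events are 21.0, 35.9 and 52.0, and power at 0.04795 is 28%, 44% and 58%.

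None of these calculations models dropout or the counting of losses to follow-up as failures. Both would tend to lower power.

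**The case against.** The strongest reply is that low power for anuria has not been demonstrated. A reader might infer from the slopes that the main comparison has some definite power well below 80% on the plan's own figures. The document does not support that. Baseline clearance, linear decline and the link from clearance to urine volume all have to be supplied from outside. Reading 0.25 wholly as true variation also implies that about 24% of 2HD patients and 9% of 3HD patients gain function (Φ(−0.18/0.25) and Φ(−0.33/0.25)). The protocol does not say whether 0.25 includes measurement error, and if much of it does, power may exceed 80%. One year is also the minimum follow-up, and longer follow-up raises power. All of this stands, so the range can only be given as an illustration.

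A reader might also infer that GFR decline is never tested. That goes too far: clearances are collected every 2 months, and the analysis section provides generic t-tests or Mann–Whitney tests for quantitative variables. What holds is that GFR decline is not a named outcome.

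Finally, one might conclude that GFR decline should become the main outcome. Replacing the main outcome after recruitment has begun in an open-label trial carries its own cost, and nothing in the document requires it.

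The mismatch itself is untouched by these points. It can be read directly from the text.

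**Conclusion.** The point holds in this form. The 80% power belongs to a comparison of mean GFR decline, and 44 per group is correct for that comparison. It does not belong to the main outcome, for which power is neither stated nor derivable. Under the assumptions in the working, with 0.25 taken wholly as true slope variation, power for anuria is roughly 30–70%. It could be 80% or more if much of the SD is measurement noise. A shortfall is plausible but not proven.

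The mismatch is certain and the size of any shortfall is not. It should be corrected because the power statement is wrong as written for the test that decides the trial, and because recruitment is tied to it.

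Separately, the paragraph gives both rates to the same arm: "0.18 mL/min/month in the 2HD group and 0.33 mL/min/month in the 2HD group". The second is evidently meant for 3HD. This is a clerical slip that changes no number and adds no weight to the main point.

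**What to change.** - In Sample size and in the Abstract, state that the 80% power refers to the difference in mean monthly GFR decline and not to the main outcome.
- In Sample size, add the power of the log-rank test for anuria with 44 per group at 0.04795, under a stated 12-month anuria rate in each arm, with a range around those rates.
- In Recruitment period, and in the matching sentence of the Abstract, reword so that reaching 44 per group is not said to secure 80% power for the main outcome.
- Optionally, name the rate of GFR decline as a secondary outcome, from the clearances already measured every 2 months. The addition should be made without sight of data by arm. The main outcome stays as it is.
- Correct the second 2HD label in Sample size to 3HD.

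The cost is wording and probably a less favourable stated power. No new data, visits or patients are needed.
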